### Intention to treat:

All patients will be accounted for at the end of the trial, i.e. according to "Intention to treat" (ITT) analysis.

## **Schedule and timeline for dissemination of the research results:**

In addition to publishing articles in international scientific journals, the project will also aim to generate informative articles, for example, articles in Norwegian journals that can be used in the primary health care. In addition, we have established a collaboration with the Norwegian Electronic Medicines Manual (NEL), and thus our research will eventually also benefit primary health service and its patients in the search for understanding of symptoms and any investigation or treatment strategy. A PhD candidate will be able to attend national and international meetings and conferences with poster presentations and participate in workshops, for example in the Society of Behavioral Medicine (SBM) and at the International Conference of CFS / ME, which will be held in 2013.

Schedule: The aim is to start processing data from the trial on 01.01.2012. The project will last for another 3 years, to 01.01.2015. Publishing: The CFS / ME project is planned to generate 3 articles in total, see below:

|                        | Spring 2012 | Fall 2012 | Spring 2013 | Fall 2013 | Spring 2014 | Fall 2014 |
|------------------------|-------------|-----------|-------------|-----------|-------------|-----------|
| Data collection | X           | X         |             |           |             |           |
| Data processing | X           | X         | X           | X         |             |           |
| Data analysis   |             | X         | X           | X         | X           | X         |
| Publications    |             | X         | X           | X         | X           | X         |

**Paper 1:** Short versus standard individual cognitive behaviour therapy for chronic fatigue syndrome: a consecutive, randomised controlled trial. *Primary outcomes are Global quality of life (SF-36), physical and mental functioning SF-36) and fatigue (Chalder Fatigue Scale). Secondary outcomes are mood (HADS), pain (NRS) and physical condition (VO2 max).*

**Paper 2:** Predictors of treatment outcome after short and standard individual cognitive behaviour therapy for patients with chronic fatigue syndrome in tertiary care: a consecutive, randomised controlled trial. Predictors: (besides the intervention): Demographics, neuropsychology, pain (NRS) and tender points, mood/psychometrics, VO2 max, tension/flexibility (GFM-52) and number of health complaints (SCL-90/SHC).

**Paper 3:** Does cognitive behaviour therapy improve physical condition and reduce fatigue in patients with chronic fatigue syndrome? The role of physical activity. If CBT improves Fatigue, is this effect mediated by improvement in VO2 max or mood? Dependent variable: Fatigue (Chalder Fatigue Scale), physical condition (indirectly Åstrand's test), depression (HADS).

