## Is cognitive behavioural therapy a good treatment for chronic fatigue syndrome?

### Summary:

The Norwegian Directorate of Health has requested documentation on treatment for chronic fatigue syndrome, CFS/ME. With this trial, The National Competence Centre for Complex Symptom Disorders (NKSL) wants to contribute to knowledge on whether cognitive behavioural therapy is good treatment for CFS/ME. Even though standard, individual CBT together with graded exercise therapy so far is the best documented treatment, there is no national or international consensus due to few randomised trials, varying quality and moderate evidence. Therefore, our goal is to test the effect of individual standard CBT, in a randomized, controlled 1-year follow-up trial. Our second goal will be to test the effect of a newly developed and shorter individual CBT (I-CBT). If the shorter therapy turns out to be as good as or better than standard CBT, the shorter therapy will be an equal and more cost-effective treatment. Patients with nonspecific fatigue will undergo a thorough, multidisciplinary assessment at the The Department for Pain and Complex Symptom Disorders (ASSL), St. Olav`s Hospital, to be diagnosed with CFS/ME or other fatigue conditions. Patients diagnosed with CFS/ME will be offered treatment in our trial with randomisation to either short I-CBT or standard individual cognitive behavioural therapy or a control group. Primary outcome measures are physical function, health related quality of life and fatigue. NKSL is a research group at ASSL, St. Olav`s Hospital that wants research to be the basis for the operation of its three outpatient clinics; the clinic for pain, the clinic for CFS/ME and the clinic for assessment to work related rehabilitation at Hysnes, Norway.

In our opinion, this study fits perfectly with the announcement:

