## Hypothesis

(1) Standard CBT (CBT) and short CBT (I-CBT) are significantly better compared to the waiting list control group (WLC) in the primary outcome measure physical function in SF-36 and in the secondary outcome measures fatigue and the rest of the SF-36 subdimensions.

(2) There is no difference in effect between I-CBT and standard CBT in the primary outcome measure physical function in SF-36 and in the secondary outcome measures fatigue and the rest of the SF-36 subdimensions.

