## Secondary research questions

(1) Which baseline factors (beyond the randomised interventions) are associated with physical function and fatigue in the entire CFS/ME selection? (2) Are the intervention effects of CBT for the primary outcome associated with equivalent changes in secondary outcome measures like fatigue, physical fitness, ability to relax, negative affect, pain and number of subjective health complaints? (3) Are the effects of CBT intervention associated with baseline factors like neuropsychological functioning, physical fitness, ability to relax or sociodemographic factors?

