#### *Primary outcome measure*

The primary outcome measure of this trial will be one of eight subdimensions, physical function, measured by "SF-36" which is a 36-item questionnaire that produces scales for both mental and physical health (19,20). The questionnaire has been used previously and is well validated in similar studies (21), is sensitive to treatment change (22) and is a sufficient measure of functional status (23).

Other outcome measures will be "Fatigue" measured by Chalder Fatigue Scale (score 0-3 with 11 items, max score/fatigue = 33 points) (24) and mental function in SF36 (0-100) (20). Outcome success criteria will be > 10 points improvement in physical function in SF36 analyzed by a 0-100 scale, where 100 is best and 0 is worst (13), 50% recovery or a score of 75 points (25).

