#### *Analyses:*

Calculation of sample size and power. We have calculated sample size assuming a mean change in SF-36 score of 10, 5, and 0 from baseline of respectively short I-CBT, standard CBT, and WLC group, a ‘within cell’ standard deviation (SD) on 15 and a correlation between baseline and post score on 0.3 (r-squared on 0.1). For a two-sided test with 5 % significance level and 80 % power, we calculated that we needed 40 patients in each group, 120 in total. Assuming a maximum drop-out level of 25 %, we calculated that we needed an additional number of 18 patients in each group, 174 patients in total. A mean change in SF-36 score of 10, 10, and 0 for short, standard, and WLC groups would increase power to 90 %.

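### The protocol contradicts itself on the primary outcome: one in the hypotheses and outcome section, three in the Summary, four in the plan for Paper 1

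*Protocol*

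**What the plan says.** The current text of the protocol gives three different accounts.

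- **One primary outcome.** The Primary outcome measure section states: "The primary outcome measure of this trial will be one of eight subdimensions, physical function". It then lists the Chalder Fatigue Scale and SF-36 mental function as other outcomes. Both statements in the Hypothesis section agree; they look for effects "in the primary outcome measure physical function in SF-36 and in the secondary outcome measures fatigue and the rest of the SF-36 subdimensions". Secondary research question 2 also classes fatigue as secondary, referring to "secondary outcome measures like fatigue, physical fitness, ability to relax, negative affect, pain and number of subjective health complaints".
- **Three.** The Summary states: "Primary outcome measures are physical function, health related quality of life and fatigue".
- **Four.** The entry for Paper 1, under the schedule and dissemination heading, states: "Primary outcomes are Global quality of life (SF-36), physical and mental functioning SF-36) and fatigue (Chalder Fatigue Scale". It leaves only mood, pain and VO2 max as secondary.

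The sample size paragraph under Analyses refers to a single score, "assuming a mean change in SF-36 score of 10, 5, and 0 from baseline", and a single error rate: "For a two-sided test with 5 % significance level and 80 % power". It does not say which SF-36 score is meant.

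**The concern.** These accounts cannot all hold. Fatigue is secondary in two places and primary in two others. SF-36 mental function is one of the other outcomes in the outcome section and primary in Paper 1. A global SF-36 quality-of-life score is primary in Paper 1, but the protocol never says how it is formed; its outcome section describes the SF-36 as eight subdimensions covering physical and mental health.

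Paper 1 is where the randomised comparison will be reported, so its list of primary outcomes bears directly on the main conclusion. The trial is not blinded for intervention and inclusion is described as nearly complete. If the conflict is still there when analysis begins, a reader of the results cannot tell which outcome was fixed in advance. A correction made after that would be hard to distinguish from a choice made with the data in view. The 5% error rate and 80% power in the sample size apply to one outcome and do not carry over to a claim based on four.

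**Working it through.** **1. Reproduce the plan's own figure.** Inputs from the sample size paragraph: mean changes 10, 5 and 0; SD 15; baseline-post correlation 0.3, with r-squared given as 0.1; two-sided 5%; 40 per group. The test is taken to be a three-group ANCOVA F-test with one covariate. The protocol does not name the test, but this one returns its figures.

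- Residual variance: 15² × (1 − 0.1) = 202.5.
- Sum of squared deviations of 10, 5, 0 from their mean of 5: 25 + 0 + 25 = 50.
- Noncentrality: 40 × 50 / 202.5 = 9.88, with 2 and 3 × 40 − 4 = 116 degrees of freedom.
- Power at 5%: **79.95%**, against the stated 80%. With r-squared 0.3² = 0.09 it is 79.5%.
- For changes of 10, 10 and 0 the sum is 66.67, the noncentrality 40 × 66.67 / 202.5 = 13.17 and the power **90.4%**, against the stated 90%.

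Both stated powers reproduce with one outcome tested once at 5%.

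**2. Error rate if several outcomes were primary and any one sufficed.** This success rule is hypothetical. The calculation uses one three-group test per outcome, at one time point, each at 5%.

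- If the outcomes were independent: 1 − 0.95³ = 14.3% for three, and 1 − 0.95⁴ = 18.5% for four.
- The outcomes are surely correlated, but the protocol gives no between-outcome correlations, so they are assumed. The table shows simulated results for large-sample three-group tests (1,000,000 draws):

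| Assumed pairwise correlation | Three outcomes | Four outcomes |
|---|---|---|
| 0.3 | 13.7% | 17.5% |
| 0.5 | 12.7% | 15.8% |
| 0.7 | 11.2% | 13.4% |

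Four outcomes therefore take the rate from 5% to about 13-18%.

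**3. Power if the multiplicity were corrected instead.** This uses Bonferroni, the 10/5/0 scenario, and the same effect size assumed for each outcome. Ranges are for r-squared 0.09 to 0.10.

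| Outcomes | Level per outcome | Power at 40 per group | Evaluable per group for 80% |
|---|---|---|---|
| 1 | 0.05 | 79.5-79.95% | about 40 |
| 3 | 0.05/3 = 0.0167 | 65% | 53 |
| 4 | 0.05/4 = 0.0125 | 61% | 56 |

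The planned 174 patients are 58 per group. With the assumed 25% drop-out, 58 × 0.75 = 43.5 would be evaluable. At 44 per group and level 0.0125, power is about 67%, so the drop-out allowance does not make up the loss.

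**The case against.** The best defence is that the sections that ought to govern agree with each other. The hypotheses and the outcome section both name SF-36 physical function, and the secondary research questions are consistent with them. The outliers are a summary and a publication plan. This stands, and it is why the repair is one of wording and its direction is clear. It does not remove the conflict, because the Paper 1 entry sets out what the main report will present as primary.

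Several stronger readings are tempting, and the protocol does not support them.

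- **That success may be claimed on whichever outcome is significant.** A reader might infer this, but no such rule is stated. The 13-18% is conditional on it. If all four had to succeed, the error rate would not inflate; power would be the problem.
- **That a multiplicity rule is missing.** Such a rule is commonly left to the statistical analysis plan, which is not at hand. Its absence here is no defect. The contradiction about what is primary remains whatever that plan says.
- **That the error rate is 23-30%, or 46-58%.** The first range also counts two separate comparisons with the waiting list, which already give 9% with a single outcome. The second adds three time points. Neither addition comes from the conflicting outcome lists. Moreover, waiting-list patients are offered I-CBT after their 16-week post-score, so three untreated control comparisons do not fit the design.
- **That the protocol fixes the primary outcome at 16 weeks.** Neither the hypotheses nor the outcome section states a time. Sixteen weeks appears as the control group's waiting period, and the Statistical analyses section leaves the months as X, Y and Z.
- **That analysis is imminent.** The timetable starts data processing on 01.01.2012 but shows data collection through Fall 2012 and analysis from Fall 2012. There is time to correct the text.

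**Conclusion.** The point holds as an internal contradiction: one, three and four primary outcomes in the current text, with fatigue and SF-36 mental function changing status between sections and one named outcome undefined. The sample size matches only the one-outcome version.

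The contradiction itself rests on no assumption. The 13-18% rests on assumed correlations of 0.7 to 0.3, one three-group test per outcome, one time point, and a success rule that the protocol does not state. The fall in power to about 61% rests on a Bonferroni correction over four outcomes and equal effect sizes. Reading the unnamed SF-36 score in the sample size as physical function is an inference from the outcome section. The matter should be settled before analysis. That conclusion follows from the conflicting definitions and does not depend on the error rates.

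**What to change.** Before analysis begins, change the Summary and the Paper 1 entry to agree with the Hypothesis and Primary outcome measure sections:

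- name SF-36 physical function (0-100) as the single primary outcome in both;
- list Chalder fatigue and SF-36 mental function as secondary in both;
- delete the global SF-36 quality-of-life score, or define how it is calculated and list it as secondary; treat the Summary's health-related quality of life in the same way.

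The choice of primary time point is a separate matter and is not part of this change.

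The cost is wording in two places, with no effect on patients, data collection or sample size: the stated 5% level and 40 per group stand as they are. What is given up is that fatigue and mental function can no longer be reported as primary results.
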